## Abstract

**Introduction:**

The prevalence of diabetes has increased worldwide, making it the most prevalent metabolic disorder. Physical inactivity contributes to the progression of this disease and aggravates other comorbidities, such as obesity and cardiovascular disease. Beneficial strategies aimed at promotion and healthy aging, oriented to decrease sedentary behavior, are necessary to obtain desirable metabolic effects and improve the quality of life of people with diabetes.

**Objective:**

To examine, through a quasi-experimental study, the effect of decreasing sedentary time and increasing motivation to adopt an active lifestyle on different clinical, anthropometric and biochemical parameters in patients diagnosed with type 2 diabetes mellitus.

**Design and methodology:**

Quasi-experimental controlled study, single-center, parallel, two-branch, with a 12-month follow-up. We plan to recruit up to a total of 169 participants, who will be assigned in a 1:1 ratio to a control group (who will receive e-mails) and an intervention group (who will receive face-to-face group and individual visits and telephone calls). The active intervention has a duration of 6 months and will be carried out by nursing professionals. The primary outcomes are sedentary time measured with the Sedentary Behavior Questionnaire (SBQ) and the use of accelerometers, and the state of motivation to change measured through the Transtheoretical Model of Physical Exercise Change Questionnaire (TMPECQ).

**Trial registration.** ClinicalTrials.gov (NCT06893146).

## Introduction

Currently, more than 463 million people worldwide suffer from diabetes [1], with type 2 diabetes accounting for 90–95% of cases [2].

A state of recurrent hyperglycemia increases the Risk of chronic complications of diabetes, which include macrovascular (CVD, peripheral vascular disease, and lower limb amputations) and microvascular (retinopathy, nephropathy, and peripheral and autonomic neuropathy) complications [3,4]. In addition, prolonged habitual sedentary behavior also increases the risk of diabetic complications, even when considering physical activity levels [5]. This means that long periods of sedentary behavior also have negative effects, regardless of compliance with established physical exercise recommendations [6]. However, there is strong evidence that the association between sedentary lifestyles and all-cause mortality is more prevalent among physically inactive individuals [7].

Worldwide, approximately 52.3% of adults with type 2 diabetes exhibit prolonged sedentary behavior, with a higher prevalence in women (60.3%) than in men (56.5%) [8]. Additionally, recent observational studies have reported daily averages of 10 hours of sedentary time in this population [9,10]. Following this global evidence, a study conducted in Spain by the Spanish Diabetes Society (SED) and the Spanish Diabetes Federation (FEDE) identified that approximately four out of ten individuals with diabetes lead a sedentary lifestyle [11]. At the local level, nearly one-quarter of the population in La Rioja exhibits high levels of sedentary behavior, with women showing a higher prevalence. These findings highlight the importance of addressing this public health issue through targeted interventions [12].

Numerous research studies support the detrimental effects of these behaviors even in non-diabetics. In a study of sedentary individuals without diabetes who engaged in sedentary behavior for an average of 9 hours per day, it was observed that adding an additional 1 hour of sedentary behavior for 8 days was associated with a 22% increase in the likelihood of developing type 2 diabetes [13].

Recent studies in adults with type 2 diabetes show that interrupting prolonged periods of sitting with light activity, such as walking at low intensity for 3 minutes every half hour for 8 hours, reduces postprandial glucose, insulin, C-peptide, and triglyceride levels [14]. Replacing sitting time with standing (2.5 hours per day) and walking at low intensity (totaling 2 hours and 20 minutes per day) every 30 minutes improves 24-hour blood glucose levels and insulin sensitivity more than structures physical exercise [15]. Stair climbing has also been shown to be effective in lowering postprandial glucose levels [16,17], although it does not have a positive impact on glycosylated hemoglobin (HbA1c) [18]. A study of young people with obesity and glucose intolerance showed that 5-minute pause intervals every hour for 12 hours were more effective in reducing blood glucose levels than 1 hour of moderate-intensity exercise at the beginning of the day [19]. Another study indicated that short but intense exercise times (6 x 1-minute brisk walk at 90% of maximum heart rate) 30 minutes before main meals improved glycemic control in people with diabetes more than a single 30-minute session of moderate-intensity walking [20]. In general, any reduction in sitting time has been shown to be beneficial for people with type 2 diabetes [21].

This shows that, in addition to exercise, reducing sedentary lifestyle has a significant impact on the health and glycemic control of people of all ages with this condition. It is essential to promote programs that modify the lifestyle of the population, addressing the adoption and long-term maintenance of habits that reduce sedentary time. In addition to increasing physical activity, it is considered necessary to implement strategies to reduce sedentary behavior. This may be a more agile objective, serving as a complementary strategy to improve both physical fitness and metabolic health in individuals with type 2 diabetes.

In this regard, the novelty of the design lies in the structured integration of educational and motivational components with a specific focus on reducing sedentary behavior, developed and implemented from nursing practice, with both in-person and telephone follow-up. This approach enables personalized, sustainable, and adaptable care within real healthcare settings, with the potential to improve adherence and quality of life in individuals with type 2 diabetes.

### Objectives

The general objective of the study is to know the effect of decreasing sedentary time and increasing motivation to adopt an active lifestyle of different health-related parameters in patients diagnosed with type 2 diabetes mellitus. Also to provide support and resources for the proper management of diabetes. Likewise, it will be verified that face-to-face interventions and telephone interventions by nursing professionals decrease the sedentary time in the diabetic population and if it means and improvement in clinical, anthropometric and biochemical parameters. Also, to evaluate the quality of life and the degree of motivation aimed at reducing sedentary time and to integrate the reduction of sedentary time in the lifestyle of the participants with practical tools and guidelines adapted to the circumstances.

## Methods and analysis

### Study design

A quasi-experimental controlled study with a 12-month follow-up will be carried out. The study has been chosen to be conducted as a single-center study for strategic and logistical reasons. A two-arm parallel design will be used. The control group (CG) will receive messages by mail with healthy lifestyle habits, while the intervention group (IG) will receive a behavioral intervention based on lifestyle modification, focusing on reducing sedentary time. These interventions will be directed by the research nurse.

### Sample and recruitment

The sample size was calculated for 230 members of the Diabetes Association of La Rioja (ASDIR) aged 18 years or older and diagnosed with type 2 diabetes mellitus.

A 95% confidence level and a 5% margin of error were used, values commonly accepted in community intervention studies [22]. Additionally, a dropout rate of 15% was anticipated, in line with that observed in previous studies conducted with populations with type 2 diabetes in similar contexts, where dropout rates range between 10% and 20% during multi-month interventions [23–26]. This estimation takes into account factors such as advanced age, disease burden, and the potential for low adherence to behavioral change programs. With these parameters, the final adjusted sample size is 169 individuals. Through a sequential allocation process based on the order of informed consent signing, approximately half will be assigned to the control group (CG) and the other half to the intervention group (IG), resulting in 84 participants in the CG and 85 in the IG.

To make it known to the associated and to know their willingness to participate, the president of the association will proceed to send emails and a broadcast message on WhatsApp through the community group. The dissemination of the project will begin in April 2025 and will last a total period of two months. Those interested and who meet the inclusion criteria will be selected during the following month for the study. A face-to-face visit will be made to the Association to explain the detailed bases of the Project and to sign the informed consent, while the group allocation will be carried out simultaneously. The study will last for a total of 12 months from the date of informed consent signature. Fig 1 presents the flowchart outlining the planned process of sample selection, recruitment, and participant allocation for this study.

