### Statistical analysis

First, a descriptive analysis of the sociodemographic, clinical and anthropometric data of the participants will be performed. Quantitative variables (such as age, BMI, glucose, cholesterol and blood pressure levels) will be described using means ± standard deviation (for those with normal distribution) and medians (with 25^th^ and 75^th^ percentiles) when they do not follow a normal distribution. Qualitative variables (such as sex, educational level, and marital status) will be described as relative frequencies, cumulative relative frequencies, and percentages. These analyses will be performed using Microsoft Excel for data organization and IBM SPSS Statistics for statistical calculations.

The normality of quantitative variables will be assessed using normality tests, such as the Shapiro-Wilk or Kolmogorov-Smirnov tests, as appropriate. To evaluate the homogeneity of variances and sphericity in repeated measures, Mauchly’s test will be applied. To evaluate the efficacy of the intervention, the two groups of the study will be compared: CG and IG at different times (T0, T1, T2, T3). For continuous variables, a repeated measures analysis of variance (repeated measures ANOVA) will be conducted, applied only if the assumptions of residual normality and sphericity are met. In case of violation of the sphericity assumption, Greenhouse-Geisser or Huynh-Feldt corrections will be used to adjust the degrees of freedom. If the variables do not meet the normality assumption or the distribution is clearly non-parametric, the non-parametric Friedman test will be employed to analyze differences between repeated measurements.

The chi-square test will be applied to compare the distribution of qualitive variables between the two groups, such as the presence of comorbidities or the level of motivation to change. To establish statistical significance, a significance level of p < 0.05 will be used.

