Regarding the handling of missing data, a descriptive analysis will be conducted to identify its pattern and proportion. An intention-to-treat (ITT) analysis will be adopted, including all participants assigned regardless of their adherence or losses during follow-up. For quantitative variables with missing data, multiple imputation will be applied using the Multiple Imputation by Chained Equations (MICE) method, generating several complete datasets that will be analyzed to improve accuracy and reduce bias. Additionally, a sensitivity analysis will be performed comparing results from imputed and complete data to assess the robustness of the conclusions.

One of the objectives of the study is to evaluate how the reduction of sedentary time is related to improvements in clinical parameters such as glucose, lipid and blood pressure levels. To this end, Pearson correlations will be used to analyze the relationship between sedentary time (measured with accelerometers) and changes in these parameters. In addition, multiple linear regression models will be used to adjust the analyses for possible covariates (age, sex, antidiabetic treatment, etc.).

Subgroup analyses based on relevant participant characteristics (such as age, sex, and level of motivation to change) will be considered exploratory and conducted with the aim of identifying possible differences in response to the intervention. To control for multiplicity across primary and secondary outcomes, the Bonferroni correction will be applied to adjust the significance level and minimize false positives. Given the relatively small number of comparisons, this conservative approach is appropriate and unlikely to substantially reduce statistical power. Results from these analyses will be interpreted with caution.

Changes in quality of life and motivation to change will be analyzed using the corresponding validated questionnaires. Both will be analyzed using repeated measures analysis of variance or linear regression to determine whether the interventions have a positive impact on these aspects over time.

The reliability and validity of the instruments used, such as the SBQ and the ActiTrainer accelerometer, have been verified. These instruments will measure sedentary lifestyle in an objective and reliable manner. On the other hand, the internal validity of the MTCEJ and DQOL Questionnaire has also been evaluated by psychometric analysis.

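### The 169 is sized to estimate one percentage among 230 members to within 5 points; that precision does not carry over to the two-group comparison the study is designed to make

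*Protocol article*

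**What the plan says.** All of the following is in the protocol article.

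- **Sample and recruitment** names the population: "The sample size was calculated for 230 members of the Diabetes Association of La Rioja (ASDIR"). It then gives the precision inputs, "A 95% confidence level and a 5% margin of error were used, values commonly accepted in community intervention studies", and the loss, "a dropout rate of 15% was anticipated". The result follows directly: "With these parameters, the final adjusted sample size is 169 individuals". Sequential allocation splits this total, "resulting in 84 participants in the CG and 85 in the IG".
- **Abstract (Design and methodology)** and **Study design** describe a controlled, parallel, two-arm study. The primary outcomes are sedentary time (questionnaire and accelerometer) and motivation to change.
- **Statistical analysis** sets the efficacy question: "the two groups of the study will be compared: CG and IG at different times (T0, T1, T2, T3"). It uses a significance level of 0.05 and applies Bonferroni across primary and secondary outcomes. It describes that correction as "unlikely to substantially reduce statistical power".

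**The concern.** A population size, a confidence level and a margin of error are the inputs for a survey that estimates one percentage in a finite population. They involve no second arm, outcome variance, target difference or power. The study nevertheless compares two arms.

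A reader who sees 95% confidence and a 5% margin next to the final number may take it that the trial was sized for its main comparison, or that its effect estimates will be precise to about 5%. Neither follows. If the result is null, the reader cannot tell from the stated basis which differences the study could have detected, and may read absence of evidence as evidence of no effect. The later reassurance about power under Bonferroni has no stated power figure behind it.

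**Working it through.** **Inputs from the article.** N = 230; 95% confidence (z = 1.96); margin e = 0.05; dropout 15%; 84 and 85 per arm.

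**Assumption.** Neither the formula nor the expected proportion is named. I take p = 0.5, the usual worst case.

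**1. Reproducing the 169.** One proportion with finite-population correction:

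n = N·z²·p(1−p) / [e²(N−1) + z²·p(1−p)]
= 230 × 3.8416 × 0.25 / (0.0025 × 229 + 3.8416 × 0.25)
= 220.89 / 1.5329 = 144.1, so 144.

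144 / 0.85 = 169.4, stated as 169. (Without rounding to 144 first, 144.1/0.85 is about 169.5.) With p = 0.4 the result is 166.9; with p = 0.3 it is about 158. The stated figure therefore points to p at or near 0.5.

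Reverse check, 144 completers out of 230: 1.96 × √[(0.25/144) × (86/229)] = 5.0 points. The 5% is correct for one percentage in all 144 completers.

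**2. The same numbers applied to two arms.** 144 completers give 72 per arm.

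- One arm, proportion: 1.96 × √(0.25/72) = 11.5 points (9.6 with the finite-population correction).
- Difference in proportions, p = 0.5: 1.96 × √(0.5/72) = 16.3 points.
- Difference in means: 1.96 × √(2/72) = 0.33 SD.
- Per-arm size for a 5-point half-width on a difference in proportions: 1.96² × 0.5 / 0.05² = 768.3, so 769, more than three times the whole membership.

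**3. Detectable difference at 72 per arm, 80% power.** Assumed analysis: two-sample t-test at one time point, two-sided, noncentral t.

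| Alpha | Detectable difference | Power for 0.47 SD |
|---|---|---|
| 0.05 | 0.47 SD | 80% |
| 0.05/3 = 0.0167 | 0.54 SD | 65% |
| 0.05/29 = 0.0017 | 0.67 SD | 36% |

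Both outcome counts are assumptions. Three takes the two sedentary-time measures and motivation as one measure each. About 29 adds four anthropometric measures (weight, BMI, waist, hip), two blood pressures, 18 laboratory values, physical activity and quality of life: 3 + 4 + 2 + 18 + 1 + 1 = 29.

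**4. Sensitivity to the analysis.** For change from baseline, the SD is multiplied by √[2(1−ρ)], where ρ is the baseline-to-follow-up correlation. The article gives no ρ, so I show a range at alpha 0.05:

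- ρ = 0.7: 0.47 × 0.775 = 0.36 SD
- ρ = 0.5: 0.47 × 1.000 = 0.47 SD
- ρ = 0.3: 0.47 × 1.183 = 0.56 SD

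**The case against.** Much can be said for the article, and several stronger readings fail.

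- **A reader might infer that 169 is miscalculated.** It is not. The inputs give 169 up to rounding, once p = 0.5 is assumed. The mismatch is between the calculation and the purpose.
- **A reader might infer that the 5% margin is false.** The article attaches it to no quantity and never claims it for the group difference. It is true for one percentage in the 144 completers. It is inapplicable to the comparison.
- **A reader might infer that the trial is underpowered.** The documents do not support this. They state no target difference, so 0.47 SD cannot be called too large or acceptable.
- **A reader might infer that power was never computed.** Only the article is at hand, so one can say only that none is stated. The Bonferroni remark concerns the loss from the correction and does not claim a power calculation.
- **The detectable differences depend on assumptions.** The plan specifies repeated-measures ANOVA over four time points and multiple imputation for all assigned participants, not a t-test in completers. That stands, and is why a range is shown and the t-test basis is labelled.
- **Alpha shared over three outcomes is not the plan's rule.** Bonferroni spans primary and secondary outcomes, and motivation is scored by stage subscale. The counts of 3 and 29 are illustrations only.
- **Confidence intervals are promised with the results.** These would limit misreading of a null finding, but they do not make the stated basis fit the comparison.

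None of this removes the core. The article sets out its basis in full and says that 169 follows from it, so this is not a detail left to a fuller document.

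**Conclusion.** The point holds as a mismatch between design and justification. The only stated basis for 169 is a single-proportion survey precision, while the study is a two-group comparison. At about 72 per arm, the between-group 95% half-width is about 16.3 points for proportions (p = 0.5) or 0.33 SD for means, and the 5% does not describe it.

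The half-widths rest on 15% loss spread evenly over the arms. The detectable differences rest also on the test, correlations and outcome counts assumed above. The identification of the formula rests on p = 0.5, but the conclusion does not depend on it: whatever p was used, the listed inputs contain nothing about a difference between groups.

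The remark that Bonferroni is unlikely to cost much power is not supported. For an effect with 80% power at 0.05, power falls to about 65% over three outcomes and 36% over 29.

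**What to change.** 1. In Sample and recruitment, keep 169 as the recruitment target (the membership allows at most 230) and remove the 5% margin of error as its justification.
2. State what 169 delivers for the intervention-control difference in a named primary outcome at a named time point: about 72 per arm after 15% loss, and 80% power for 0.47 SD at two-sided 0.05 under a single-time-point t-test. If change from baseline is analysed, give about 0.36 to 0.56 SD for correlations of 0.7 to 0.3, or one figure with a justified correlation. Translating SD units into sedentary time needs an SD that the article does not supply; the authors should state one with its source.
3. Give the same figure at the Bonferroni alpha actually applied across primary and secondary outcomes, with the number of outcomes counted explicitly.
4. In Statistical analysis, replace the statement that Bonferroni is unlikely to reduce power much with the computed loss for that number of outcomes.

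Cost: one paragraph and one sentence rewritten, with no change to participants or procedures. The downside is that the stated precision becomes less favourable than the present text suggests.

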### Group allocation and masking

The distribution in the CG or IG will be performed sequentially in a 1:1 ratio in order of access to the study, i.e., the first patient who accepts the informed consent will be included in the IG, the next in the CG and so on until the sample is complete. This sequential assignment does not constitute strict randomization, and concealment techniques will not be employed. While this methodology is appropriate for research in real clinical settings, it may carry a risk of selection bias. This risk is acknowledged and will be considered when interpreting the results.

Due to the nature of the intervention, both the participants and the nursing staff and collaborating personnel will be aware of the assigned groups.

Additionally, the principal investigator will be responsible for data collection and analysis; therefore, outcome assessor blinding will not be applied.

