**Fig 3 pone.0330393.g003:**
[figure not shown]
Nursing interventions for the intervention group.

Measurements for all participants in the CG and the IG are taken at the beginning of the study (T0), at 3 months (T1), at an intermediate phase (6 months, T2) and at 12 months from the beginning of the study (T3). Once the 12 months have elapsed, the study will be terminated. By then, data collection will have been completed, and the results are expected to be available within the following 3 months.

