### Ethical approval

The present study is approved by the Ethics Committee for Drug Research in La Rioja (Ref. CEImLAR PI 778) and will comply with all established ethical standards. Healthcare professionals participating in the study will sign a document in which they undertake to protect the confidentiality of all patients. Before any procedure is performed, free and voluntary written informed consent must be obtained from each patient, which may be voluntarily revoked at any time during the study.

The information obtained in the study will be confidential and stored in coded form in an automated data file. The guidelines established in the Declaration of Helsinki, the current ethical guidelines for research involving human subjects and the Data Protection Act and the legislation in force in Spain will be followed. The processing of personal data of all patients will comply with the provisions of the Organic Law 3/2018 of December 5, 2018, on the Protection of Personal Data and Guarantee of Digital Rights and the provisions of Regulation (EU) 2016/679 of the European Parliament and of the Council of 27 April 2016 on Data Protection (GDPR). Our study design respects fundamental ethical principles and protects the welfare and rights of all participants.

Monitoring, audits, CEImLAR reviews and regulatory inspections will be allowed with the study, providing direct access to the original data.

Ethical audits are expected to be conducted annually and at the conclusion of the study. The research team will notify the ethics committee of any substantial protocol modifications through a written report sent via email, for evaluation and approval prior to implementation.

In the event of significant changes affecting participants, these will be communicated directly to them, and their informed consent will be requested again if necessary.

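### Allocation is made openly at consent, hence before T0, and nothing in the text keeps the group from participants or staff until the baseline of the reactive primary outcomes is complete

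*Protocol article*

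**What the plan says.** Sample and recruitment in the protocol article describes one visit to the Association at which the project is explained. Participants attend "to sign the informed consent, while the group allocation will be carried out simultaneously". Ethical approval adds: "Before any procedure is performed, free and voluntary written informed consent must be obtained from each patient".

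Group allocation and masking gives the rule, applied until recruitment ends: "the first patient who accepts the informed consent will be included in the IG, the next in the CG and so on until the sample". It continues: "This sequential assignment does not constitute strict randomization, and concealment techniques will not be employed". On awareness it says that "both the participants and the nursing staff and collaborating personnel will be aware of the assigned groups", and that "outcome assessor blinding will not be applied", because the principal investigator collects and analyses the data.

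The Abstract names the primary outcomes: "The primary outcomes are sedentary time measured with the Sedentary Behavior Questionnaire (SBQ) and the use of accelerometers", together with motivation to change on the TMPECQ. Study activities says that measurements in both groups "are taken at the beginning of the study (T0") and again at 3, 6 and 12 months. Level of sedentary lifestyle has the study nurse place the accelerometer, which is worn for 5 consecutive days in each measurement period. Statistical analysis compares the groups over T0, T1, T2 and T3 by repeated-measures ANOVA.

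**The concern.** A baseline should be recorded before anyone can react to the assignment. Here it is recorded afterwards, and the primary outcomes are of the kind that reacts: two self-reports and one record of voluntary behaviour.

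Someone who knows that a nurse-led programme to reduce sitting is coming may sit less while wearing the device, or may answer the SBQ and TMPECQ differently. Someone who knows that only e-mails are coming may react differently or not at all. Staff who know the arm may also influence how the device and questionnaires are introduced.

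This differs from the selection risk that the article acknowledges, because it would arise even if the two groups were perfectly comparable at enrolment. It also makes that risk harder to judge. A T0 difference could reflect who entered each arm or how each arm reacted, and the data could not separate the two.

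**Working it through.** **Order of events, from the text**

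1. Allocation takes place at the same time as the consent signature (Sample and recruitment).
2. No study procedure precedes consent (Ethical approval).
3. From 1 and 2, all T0 study measurements, including the whole 5-day accelerometer record, come after allocation.
4. Allocation is fixed alternation with the first consenter in the IG, without concealment. Participants, nurses and collaborating personnel know the group, and there is no assessor blinding (Group allocation and masking).
5. No sentence withholds the group until T0 is complete. The moment of disclosure is not stated. The first group session falls in month 1 (Study activities), but its order relative to T0 is not stated either.

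**Effect on the comparison**

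Let r be the between-arm difference in T0 caused by knowing the group, with follow-up values unaffected, and rho the correlation between T0 and follow-up (equal variances).

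- Change contrast, (follow-up − T0) in IG minus the same in CG: bias of size r.
- Baseline-adjusted contrast, follow-up difference minus rho × T0 difference: bias of size rho × r.

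The sign depends on the reaction. If IG members sit less at T0, the apparent reduction shrinks. If they report more sitting at T0, it grows.

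**Scale, on assumed inputs only**

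The article gives no SD, no correlation and no estimate of r. Assume no true effect, one follow-up time, SD 1, 84 per arm (the article plans 84 and 85) and two-sided alpha 0.05 without Bonferroni correction. The SD of a change is √(2(1−rho)), the residual SD after adjustment is √(1−rho²), and SE = SD × √(2/84). For bias b, the rejection rate is Φ(b/SE − 1.96) + Φ(−b/SE − 1.96).

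| rho | r (SD) | Change: bias | Change: false rejection | Adjusted: bias | Adjusted: false rejection |
|---|---|---|---|---|---|
| 0.5 | 0.1 | 0.10 | 9.9% | 0.05 | 6.6% |
| 0.5 | 0.2 | 0.20 | 25.4% | 0.10 | 11.6% |
| 0.5 | 0.3 | 0.30 | 49.4% | 0.15 | 20.2% |
| 0.7 | 0.1 | 0.10 | 13.3% | 0.07 | 9.7% |
| 0.7 | 0.2 | 0.20 | 38.7% | 0.14 | 24.6% |
| 0.7 | 0.3 | 0.30 | 70.9% | 0.21 | 47.8% |

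Example, rho 0.5 and r 0.2, change contrast: SD = 1, SE = √(2/84) = 0.154, b/SE = 1.30, rejection 25.4%. With 72 per arm (after about 15% loss) this becomes 22.4%.

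**The plan's own figure**

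The sample size of 169 is not affected. A finite-population formula with N = 230, a 5% margin and p = 0.5 (assumed) gives 144, and 144/0.85 = 169.4.

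**The case against.** The strongest reply is that the text fixes when the group is assigned, not when it is disclosed. The awareness statement carries no time, and Figs 1 and 2, which may show the sequence, are not available here. This is correct. A reader might infer that participants are told their group at the consent visit. Open alternation makes that likely, but the documents do not say it.

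A reader might also infer that the baseline is already contaminated by the intervention. The documents do not support that either. T0 is placed at the start of the study, and no text puts an intervention contact before it. What is shown is a risk, not an established bias.

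Nor are all T0 variables equally exposed. A few days of knowing the group is unlikely to move HbA1c, lipids or anthropometry much, and the IPAQ asks about the last 7 days, which may partly precede allocation.

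Only the difference between arms matters. Both arms hear about the project, are trained on the device and wear it, so a shared reaction cancels. Finally, the article already concedes the lack of blinding and of guaranteed baseline comparability.

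These points limit the claim but do not remove it. Allocation before T0 is stated, nothing in the text protects T0 from knowledge of the group, and the limitations in the Discussion do not mention a baseline taken after allocation.

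**Conclusion.** The concern holds as a weakness in the stated order. Assignment precedes T0 and is unconcealed, and nothing in the text prevents participants or staff from knowing the arm while the accelerometer record, SBQ and TMPECQ are collected. Any between-arm reaction r passes into the T0–T3 comparison, in full for a change contrast and by about rho × r after baseline adjustment. Adjustment therefore reduces the bias without removing it.

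Neither the size nor the direction of r can be obtained from the documents. The rejection rates above show sensitivity under assumed inputs and do not predict this trial's result. Any statement that a given share of the effect is lost would likewise rest on assumptions alone. If IG members sit less during T0, the bias would hide a benefit rather than create one.

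The point deserves action because a baseline that has reacted to assignment cannot be recovered later, whereas preventing it is cheap. If T0 is in fact completed before anyone learns the group, a statement of that order, reconciled with allocation at consent, would settle the matter.

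**What to change.** Amend Sample and recruitment and Group allocation and masking, and the flow figures if they show otherwise, so that the order is:

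1. written consent;
2. completion of T0, including the returned accelerometer and all questionnaires;
3. group assignment and disclosure, for example by applying the 1:1 sequence in order of T0 completion;
4. first group session.

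Moving only the disclosure is not enough. Under strict alternation with the first consenter in the IG, the consent sequence number reveals the arm to staff, and to any participant who knows their place in the order. The assignment itself must follow T0.

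Two details should be fixed at the same time. Define T0 as closed when the device and questionnaires are returned, so that assignment does not depend on whether the record later proves valid. Also state, identically for both arms, which date starts the clock for T1 to T3, since the article now counts the study from the consent signature.

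The cost is a delay of at least the 5-day wear period between consent and assignment, and some scheduling work around devices and health-centre measurements. The sample size does not change. Alternation remains predictable, so the acknowledged selection risk is not cured by this change.

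If T0 has already been collected, report each participant's interval from allocation to T0 and name the post-allocation baseline as a limitation.
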